### Aim 1: Examine the Effect of RT on HRQOL Trajectory Over Time

#### Study Design and Study Population

A retrospective cohort study design is planned for Aim 1. Older women who were enrolled in Medicare and completed the MHOS between 1998 and 2016 are eligible for the study. The inclusion criteria were as follows: (1) a diagnosis of primary breast cancer between 1998 and 2014 and reported to SEER, (2) low-risk breast cancer, including early-stage (T1-2N0), ER-positive, and node-negative, (3) ≥65 years of age at diagnosis (with 65 years being the threshold for Medicare eligibility), (4) receipt of BCS (lumpectomy, quadrantectomy, or partial mastectomy) as primary treatment for breast cancer, and (5) completion of at least 1 MHOS assessment before and after breast cancer diagnosis to allow for assessing the change in HRQOL. Cases were excluded if they (1) had a previous cancer diagnosis (other than nonmelanoma skin cancer), (2) had more than 1 primary tumor at diagnosis, (3) received treatment outside of standard time frames (ie, treatment initiated 1 year after cancer diagnosis), (4) received RT before surgery, or (5) tumor histology was other than carcinoma. While these eligibility criteria may reduce external validity, they will enhance internal validity.

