Few studies have investigated the effect of RT among older women with varying comorbidity burden, and to our knowledge, none of the previous studies have evaluated long-term HRQOL trajectories post RT within older women treated in the modern era. Thus, the proposed study aims to examine the effects of RT on long-term HRQOL trajectories and survival outcomes among older women with low-risk breast cancer in an observational setting. Minimizing the potential bias due to treatment selection and controlling for potential differences in confounding factors between treatment groups are essential in observational comparative effectiveness studies without randomized treatment [30]. To mitigate this concern, first, we will only select older women with low-risk breast cancer whose main treatment plan includes BCS and endocrine therapy with RT being an option. Among this group of women, only 3.3% undergo chemotherapy [1]; thus, the confounding effect of chemotherapy on HRQOL and survival outcomes is minimal. Second, to further balance out the potential confounding factors between the 2 groups, we will use inverse probability of treatment weighting (IPTW) methods, a type of propensity score analysis [31-34], which we have applied successfully in other projects [35,36]. All potential confounding variables will be included in the statistical models when deriving the weights for each group.

This comparative effectiveness study will utilize a national sample of older women to provide much-needed evidence regarding the combined effects of RT and comorbidity on HRQOL (subjective outcome) and survival (objective outcome) in older women. This research has 2 aims.

Regarding Aim 1, we will examine the effect of RT on the HRQOL trajectory over time and its interaction with comorbidity burden in older women with low-risk breast cancer (n=465) using IPTW-adjusted growth mixture models. We hypothesize that the HRQOL trajectory will differ by treatment status and comorbidity burden, and the largest decline will be observed in older women with the highest comorbidity burden.

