Regarding Aim 2, we will examine the effect of RT on 5-year mortality and its interaction with comorbidity burden in older women with low-risk breast cancer (n=634) using Kaplan-Meier survival analysis and a IPTW-adjusted Cox regression model. We hypothesize that receiving adjuvant RT will improve 5-year mortality, but the magnitude of improvement will differ by comorbidity burden class. We expect that women who have the lowest comorbidity burden and also receive RT will experience the greatest improvement in survival outcomes.

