#### Measurements

The primary exposure variable will be adjuvant RT. We will consider BCS alone and BCS with adjuvant RT as the treatments. The SEER data provide information on radiation treatment and the sequence of surgery and radiation.

The outcomes of Aim 1 will be HRQOL scores measured over a 5-10 years of follow-up (ie, prediagnosis through post-treatment). MHOS measures HRQOL using the Medical Outcomes Study 36-item Short Form (SF-36) through the year 2005 and the Veterans RAND 12-item Health Survey (VR-12) from the year 2006 onwards. These 2 questionnaires have been validated in many languages and are widely used in HRQOL research, including that involving breast cancer patients [38]. The NCI developed algorithms to convert SF-36 scales to VR-12 scales; hence, the latter will be used across all cohorts in the current study. The VR-12 items correspond to 8 health domains, namely physical functioning, role limitations due to physical problems, role limitations due to emotional problems, bodily pain, social functioning, mental health, vitality, and perceptions of general health. These 12 items are then summarized into 2 summary scores: the physical component summary score and the mental component summary score. These 2 summary scores are standardized scores (mean 50, SD 10), which are normed based on the general US population. A total of 465 women who met the eligibility criteria for Aim 1 completed MHOS multiple times (an average of 3 times). We will sort the data according to the prediagnosis (T_0_) and postdiagnosis (T_1_…T_10_) timelines, specifying the time lapse from the cancer diagnosis. The prediagnosis HRQOL (T_0_, n=465) will be assessed using the survey conducted within 24 months prior to the diagnosis date recorded in SEER. The postdiagnosis HRQOL (T_1_…T_10_) will be assessed using the survey completed after the diagnosis of breast cancer. We collected 465 data points for the precancer diagnosis, 508 data points within 2 years postdiagnosis, 166 data points for 2-<5 years postdiagnosis, and 92 data points for ≥5 years postdiagnosis. The number of patients who completed MHOS in each time frame is presented in Table 1.

**Table 1 table1:** Number of patients who completed MHOS in each time frame (N=465).

Survey time to cancer diagnosis (months), t	Prediagnosis and postdiagnosis HRQOL timelines	n (%)
–24<t<0	T_0_	465 (100)
0≤*t*<12	T_1_	253 (54)
12≤*t*<24	T_2_	255 (55)
24≤*t*<36	T_3_	79 (17)
36≤*t*<48	T_4_	50 (11)
48≤*t*<60	T_5_	37 (8)

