### Aim 2: Examine the Effect of RT on Breast Cancer-Specific Mortality

#### Study Design and Study Population

A retrospective cohort study design will be used in the context of Aim 2. Older women who were enrolled in Medicare and completed the MHOS will be selected for this study. The inclusion criteria were (1) a diagnosis of primary breast cancer between 1998 and 2010 (to ensure at least 5 years of follow-up after a cancer diagnosis) and report to SEER, (2) a diagnosis of low-risk breast cancer, (3) ≥65 years of age at diagnosis given the Medicare framework, (4) receipt of BCS (lumpectomy, segmental resection, quadrantectomy, or partial mastectomy) as primary treatment for breast cancer, and (5) completion of at least 1 MHOS within 24 months prior to breast cancer diagnosis (to allow the evaluation of the prediagnosis comorbidity burden). Participants will be excluded from the study if (1) they had a previous cancer diagnosis (other than nonmelanoma skin cancer), (2) they had more than 1 primary tumor at diagnosis, (3) they received treatment outside of standard time frames (ie, treatment initiated 1 year after cancer diagnosis), (4) they received RT before surgery, or (5) their vital status was missing.

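### Aim 1 entry requires a survey after diagnosis: about a quarter or more of women with a baseline survey are left out, a selection risk that the planned weights do not address

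*Protocol article*

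**What the plan says.** All references are to the Protocol article.

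- **Aim 1, Study Design and Study Population.** The diagnosis window is "a diagnosis of primary breast cancer between 1998 and 2014 and reported to SEER". The fifth inclusion criterion is "completion of at least 1 MHOS assessment before and after breast cancer diagnosis to allow for assessing the change in HRQOL". The same paragraph ends by saying that the criteria may cost external validity but will gain internal validity.
- **Aim 1, Measurements.** "A total of 465 women who met the eligibility criteria for Aim 1 completed MHOS multiple times". All 465 have a survey in the 24 months before diagnosis (T0; Table 1 shows 100%).
- **Aim 2, Study Design and Study Population.** The window is shorter: "a diagnosis of primary breast cancer between 1998 and 2010 (to ensure at least 5 years of follow-up after a cancer diagnosis". The survey criterion is only "completion of at least 1 MHOS within 24 months prior to breast cancer diagnosis".
- **Introduction.** Aim 1 is to be studied "in older women with low-risk breast cancer (n=465) using IPTW-adjusted growth mixture models", Aim 2 "in older women with low-risk breast cancer (n=634) using Kaplan-Meier survival analysis".
- **Aim 1, Statistical Analysis Plan.** The weights are the inverse probability of the treatment received. The predictors listed for them include neither comorbidity class nor T0 HRQOL. The growth model regresses each woman's intercept and slope on RT and comorbidity class, with adjustment for confounders.
- **Aim 2, Statistical Analysis Plan.** The sensitivity analysis for informative censoring is described here and not under Aim 1.
- **Methods, Overview.** MHOS has two waves two years apart, the second is not always completed, and only some women are sampled into more than one cohort.

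**The concern.** A post-diagnosis survey is an event after the index date. To have one, a woman must be alive, still enrolled, sampled, and well and willing enough to answer. Choosing the cohort on such an event can distort the comparison of RT with no RT when the event depends on both RT and health.

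The protocol supplies both links. The Introduction hypothesizes that RT improves 5-year mortality. Aim 1, Measurements says that comorbidity probably worsens HRQOL and survival and also influences the treatment decision. If both are true, the untreated women who remain could be the healthier ones, and RT would look worse for HRQOL than it is. The women with the highest comorbidity burden, in whom Aim 1 predicts the largest decline, may also be those most often lost.

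Weights for receipt of RT, fitted only among women who met the criterion, balance the groups within the selected set. They do not undo the selection.

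**Working it through.** **1. The plan's own counts (Table 1).** 253 + 255 = 508; 79 + 50 + 37 = 166; 29 + 21 + 17 + 8 + 17 = 92. These match the text. The total is 766 post-diagnosis surveys, and (465 + 766)/465 = 2.65 surveys per woman, consistent with the stated average of 3.

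**2. Gap between the two cohorts.** Both need a survey in the 24 months before diagnosis. The Aim 2 window (1998–2010) lies inside the Aim 1 window (1998–2014). 634 − 465 = 169, and 169/634 = 26.7%.

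**3. How firm that share is.** Let h be the proportion of the 634 with non-carcinoma histology (an exclusion listed for Aim 1 only) and N2 the number of women with a T0 survey diagnosed in 2011–2014. Neither is given.

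Share left out = 1 − 465/(634 × (1 − h) + N2)

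| Assumption | Share left out |
|---|---|
| h = 0, N2 = 0 | 26.7% |
| h = 1%, N2 = 0 | 25.9% |
| h = 2%, N2 = 0 | 25.2% |
| h = 5%, N2 = 0 | 22.8% |
| h = 0, N2 = 98 (half the 1998–2010 rate) | 36% |
| h = 0, N2 = 195 (same rate, 634 × 4/13) | 44% |
| h = 0, N2 = 293 (1.5 times the rate) | 50% |

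N2 = 0 is the extreme case in which no eligible woman was diagnosed after 2010. The other listed difference, missing vital status (an Aim 2 exclusion only), could only raise the share. The comparison assumes that both aims define low-risk disease and breast-conserving surgery alike. The Aim 2 list of procedures also names segmental resection.

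**4. What scheduling could explain.** A woman whose T0 survey was a first wave is due her second wave within about 24 months after diagnosis. A woman whose T0 survey was a second wave has nothing further scheduled unless she is resampled. Table 1 fits this pattern: 508 of 766 post-diagnosis surveys (66%) fall in months 0 to <24, and the count drops from 255 to 79 in the next year. The protocol does not split the gap by cause.

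**5. When selection would bias the RT contrast.** This illustration uses assumed inputs: no true RT effect, HRQOL SD 10, equal groups, and logistic selection on HRQOL and RT.

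- Selection on health only, or on RT only: bias 0.
- Selection on both (log-odds 0.3 to 1.0 per SD of HRQOL, odds ratio 1.25 to 2.0 for RT): −0.1 to −0.9 points with 73% selected, and −0.2 to −1.1 points with 56% selected.
- For scale, the standard error of a simple 1:1 mean difference with 465 women is 10 × √(2/232.5) = 0.93.

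This shows the condition for bias. It does not estimate the bias in this study.

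**The case against.** The strongest reply is that the two-wave design alone could produce the whole gap. Loss by survey calendar need not bias the RT contrast, and no documented number of women is shown to be lost to death or illness. This stands, and it limits the claim to a risk.

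The growth model already adjusts for RT, comorbidity class, age and year of diagnosis. A response weight therefore adds mainly T0 HRQOL and survey wave, and cannot repair selection on unmeasured health after diagnosis. That also stands, but those two variables are information that the plan does not use.

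The protocol concedes reduced external validity, and response weights, estimand wording and non-response tables are commonly left to a fuller document. That is fair for those details. The eligibility rule and the internal-validity claim, however, are fixed in this article.

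A reader might infer more than the documents support:

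- **That 27% were removed by an event after treatment.** The criterion is post-diagnosis. T1 starts at month 0 and only treatment starting a year after diagnosis counts as too late, so some qualifying surveys can precede RT.
- **That 27% is a strict minimum.** The histology exclusion could bring it somewhat lower.
- **That the RT contrast is biased, or decline at high burden understated, by a known amount.** No passage gives response by RT group or comorbidity class.

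**Conclusion.** The concern holds as a design risk. Criterion 5 makes Aim 1 entry depend on events after the index date. About a quarter or more of women with a qualifying baseline survey are left out: 26.7% on the stated counts, about 23–26% if 1–5% of the 634 are non-carcinoma and no 2011–2014 women are added, and more when those women are counted.

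An unknown part is survey scheduling and need not matter. The remainder is death, leaving the plan or non-response. On the protocol's own hypotheses this may depend on both RT and health, so the RT contrast could be biased, by an amount that cannot be derived from the documents. The Aim 1 analysis described does not address it, and the statement that the criteria improve internal validity is not supported for criterion 5.

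**What to change.** 1. Define the Aim 1 cohort by the T0 survey alone, for diagnoses in 1998–2014, and fit the propensity model in that cohort.
2. Keep women with only a T0 survey in the growth model. T0 is already one of its time points, and the model was chosen because women are surveyed at different times. Those diagnosed in 1998–2010 are already in the Aim 2 data.
3. Multiply the treatment weight by an inverse-probability-of-response weight for having a post-diagnosis survey while alive. Predictors: RT, comorbidity class, T0 physical and mental summary scores, age, year, and whether T0 was a first- or second-wave survey. Alternatively, use a joint model with death as a sensitivity analysis.
4. Tabulate not scheduled, died and non-response by RT group and comorbidity class.
5. Limit the internal-validity statement so that it does not cover criterion 5.

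The cost is one more model, largely on data already obtained, and somewhat more variable weights. Selection on unmeasured health after diagnosis would remain uncorrected and should be stated as a limitation.

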#### Measurements

The primary exposure variable will be adjuvant RT. We will consider BCS alone and BCS with adjuvant RT as the treatments. The SEER data provide information on radiation treatment and the sequence of surgery and radiation.

The outcomes of Aim 1 will be HRQOL scores measured over a 5-10 years of follow-up (ie, prediagnosis through post-treatment). MHOS measures HRQOL using the Medical Outcomes Study 36-item Short Form (SF-36) through the year 2005 and the Veterans RAND 12-item Health Survey (VR-12) from the year 2006 onwards. These 2 questionnaires have been validated in many languages and are widely used in HRQOL research, including that involving breast cancer patients [38]. The NCI developed algorithms to convert SF-36 scales to VR-12 scales; hence, the latter will be used across all cohorts in the current study. The VR-12 items correspond to 8 health domains, namely physical functioning, role limitations due to physical problems, role limitations due to emotional problems, bodily pain, social functioning, mental health, vitality, and perceptions of general health. These 12 items are then summarized into 2 summary scores: the physical component summary score and the mental component summary score. These 2 summary scores are standardized scores (mean 50, SD 10), which are normed based on the general US population. A total of 465 women who met the eligibility criteria for Aim 1 completed MHOS multiple times (an average of 3 times). We will sort the data according to the prediagnosis (T_0_) and postdiagnosis (T_1_…T_10_) timelines, specifying the time lapse from the cancer diagnosis. The prediagnosis HRQOL (T_0_, n=465) will be assessed using the survey conducted within 24 months prior to the diagnosis date recorded in SEER. The postdiagnosis HRQOL (T_1_…T_10_) will be assessed using the survey completed after the diagnosis of breast cancer. We collected 465 data points for the precancer diagnosis, 508 data points within 2 years postdiagnosis, 166 data points for 2-<5 years postdiagnosis, and 92 data points for ≥5 years postdiagnosis. The number of patients who completed MHOS in each time frame is presented in Table 1.

**Table 1 table1:** Number of patients who completed MHOS in each time frame (N=465).

Survey time to cancer diagnosis (months), t	Prediagnosis and postdiagnosis HRQOL timelines	n (%)
–24<t<0	T_0_	465 (100)
0≤*t*<12	T_1_	253 (54)
12≤*t*<24	T_2_	255 (55)
24≤*t*<36	T_3_	79 (17)
36≤*t*<48	T_4_	50 (11)
48≤*t*<60	T_5_	37 (8)
60≤*t*<72	T_6_	29 (6)
72≤*t*<84	T_7_	21 (5)
84≤*t*<96	T_8_	17 (4)
96≤*t*<108	T_9_	8 (2)
108≤t	T_10_	17 (4)

We considered comorbidity burden as the effect modifier. Prediagnosis comorbidity is an important component of this study, as it likely impacts HRQOL and survival outcomes adversely while also affecting treatment decisions. The presence and number of comorbidities as well as their severity are important. However, the severity of each comorbidity is not available from MHOS, whereas the functional limitations and symptoms related to these comorbidities are. To account for functional limitations and symptoms as a component of comorbidity, we created a new variable named “comorbidity burden class” with 24 self-reported items (ie, 12 chronic medical conditions, 7 functional difficulties, and 5 symptoms) in MHOS (Textbox 1) using latent class analysis. This technique has been applied successfully to identify healthy patients or comorbidity profiles of cancer patients in studies using SEER-MHOS and the National Cancer Database [39,40] when the severity of comorbid conditions is not available. To identify the prediagnosis comorbidity burden class, the survey completed within 24 months before cancer diagnosis was evaluated. Latent class analysis is a subset of structural equation modeling, which is used to categorize subjects into a set of homogeneous groups (eg, k distinct membership classes of comorbidity) according to the observed variables (eg, self-reported chronic medical conditions, functional status, and symptoms). We anticipated that this procedure would suggest 3-5 distinct categories. We selected the most parsimonious number of classes using the Bayesian information criterion to find the best fitting numbers of classes. The classes of comorbidity burden will be tested as effect modifiers.

Items included in latent class analysis modeling for comorbidity burden class.

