Regarding the estimation of RT and comorbidity effects on HRQOL trajectory, we will use a multilevel growth mixture model with surveys clustered within the women to test whether a difference exists in the patterns of HRQOL trajectories with receipt of RT and comorbidity class after controlling for confounders. At level 1, we will first regress woman i’s HRQOL change, which describes how each woman’s HRQOL depends on time t. This procedure will provide the intercept and slope of the time predictor for each woman. At level 2, we will regress each woman’s intercept and slope on her RT treatment (yes/no) and comorbidity class, adjusted for confounders. This procedure will feature how individual HRQOL change trajectories vary across treatment groups (RT) and comorbidity burden classes (COM). Equation (1) presents a simplified model with no covariates, predicting HRQOL from years after diagnosis (TIME), radiation treatment (RT), and comorbidity class (COM). It will estimate the intercepts and slopes for the group of women.

HRQOL_ti_ = γ_00_ + γ_01_RT_it_ + γ_02_COM_i_ + γ_10_TIME_it_ + γ_11_RT_i_TIME_it_ + γ_12_COM_i_TIME_it_ + error **(1)**

where

γ_00_=Estimated average HRQOL in the year of diagnosis for women who did not receive RT

γ_01_=Value added to the average HRQOL if the women received RT

γ_02_=Value added to the average HRQOL due to the comorbidity class

γ_10_=Change in HRQOL for all women for each year from diagnosis

γ_11_=Additional change for each year if the women received RT

γ_12_=Additional change for each year due to the comorbidity class

A significant negative value on γ_11_ will indicate that women who receive RT experience steeper declines in HRQOL over time than those who did not receive RT, while a significant negative value on γ_12_ will indicate stronger HRQOL declines due to the comorbidity burden.

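### Aim 1 times surveys from diagnosis but codes RT as fixed per woman, so some first-year surveys taken before RT count as RT outcomes; level contrasts shrink, the tested slope does not

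*Protocol article*

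**What the plan says.** **Survey timing.** Aim 1, Measurements, sorts surveys by "specifying the time lapse from the cancer diagnosis". T0 is a survey in the 24 months before diagnosis. T1 to T10 are post-diagnosis, and each "will be assessed using the survey completed after the diagnosis of breast cancer". Table 1 opens T1 at month 0 and closes it before month 12. The same section describes the overall outcome span as "ie, prediagnosis through post-treatment".

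**Eligibility.** Aim 1, Study Design and Study Population, criterion 5 requires "completion of at least 1 MHOS assessment before and after breast cancer diagnosis". Exclusion 3 removes women who "received treatment outside of standard time frames (ie, treatment initiated 1 year after cancer diagnosis". The next exclusions read "4) received RT before surgery, or (5) tumor histology was other than carcinoma", so RT always comes after surgery. No rule places a survey after the start or end of RT.

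**Model.** Aim 1, Statistical Analysis Plan, regresses each woman's "intercept and slope on her RT treatment (yes/no) and comorbidity class", with TIME in years after diagnosis. The RT main effect γ01 is read as the amount added to average HRQOL by RT. A significant negative RT-by-time slope γ11 is read as a steeper decline with RT.

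**The concern.** A woman surveyed in month 1 and irradiated in month 3 is eligible and is coded RT = yes. Her T1 score then counts as an outcome of a treatment she had not yet received. If T1 is her only post-diagnosis survey, both of her surveys precede the exposure.

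T1 is one of the two largest post-diagnosis cells. The early part of the trajectory therefore mixes RT women not yet irradiated with RT women during or after treatment. At stake are any early or average RT-versus-no-RT level contrast, the reading of γ01 as an RT effect, and the shape of the trajectory in the first year.

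**Working it through.** **1. The plan's own counts.** From Table 1:
- T1+T2 = 253+255 = 508
- T3 to T5 = 79+50+37 = 166
- T6 to T10 = 29+21+17+8+17 = 92

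These match the text: "508 data points within 2 years postdiagnosis, 166 data points for 2-<5 years postdiagnosis, and 92 data points for ≥5 years postdiagnosis". The post-diagnosis total is 508+166+92 = 766.

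**2. Surveys that can precede RT.**
- T1 share of all post-diagnosis surveys: 253/766 = 33.0%
- T1 share within 2 years: 253/508 = 49.8%
- Surveys from month 12 on: 766-253 = 513
- Women with no T2 survey: 465-255 = 210, the upper bound on women with nothing after T1

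**3. Share that does precede RT (assumed).** Let L be the months from diagnosis to RT start, which the plan does not give. Assume that T1 surveys are spread evenly over 0-12 months and that RT women have the Table 1 distribution. The near-equal T1 and T2 counts fit an even spread but do not prove it. The pre-RT share of T1 is L/12. If the RT effect is constant once RT has begun, the level contrast shrinks by 253(L/12)/766 overall and by 253(L/12)/508 within 2 years.

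| L (months) | Pre-RT share of T1 | Overall shrinkage | Within-2-year shrinkage |
|---|---|---|---|
| 1 | 8.3% | 2.8% | 4.2% |
| 3 | 25% | 8.3% | 12.5% |
| 6 | 50% | 16.5% | 24.9% |
| 12 | 100% | 33.0% | 49.8% |

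An assumed persistent 3-point drop would average -3×(1-0.083) = -2.75 at L = 3 and -3×(1-0.165) = -2.50 at L = 6. As counts, 253×3/12 = 63 and 253×6/12 = 127 surveys are upper bounds, reached only if every woman had RT.

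**4. Effect on the slope.** A straight line was fitted by weighted least squares to an assumed RT-minus-no-RT curve. Weights were the Table 1 counts spread evenly within each window, T10 was treated as months 108-120, and L was 6 months. Each cell shows the result with, then without, the pre-RT post-diagnosis surveys.

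| Assumed effect of RT | γ11 per year, T0 in the model | γ11 per year, post-diagnosis only |
|---|---|---|
| Persistent 3-point drop | -0.455 / -0.436 | -0.207 / 0.000 |
| Gradual loss of 0.5 per year | -0.383 / -0.379 | -0.491 / -0.500 |
| 3-point drop for 1 year only | 0.000 / 0.010 | 0.257 / 0.406 |

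For the persistent drop, γ01 is -1.10 with and -1.26 without the pre-RT surveys when T0 is in the model. In the post-diagnosis-only fit it is -2.05 against -3.00.

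**The case against.** A reader might infer that pre-RT surveys dilute the RT slope and could by themselves produce a finding of no HRQOL cost. The documents do not support this. The conclusion rests on γ11, and with T0 in the model, which the stated outcome span implies, γ11 hardly moves under any of the three assumed curves. In a post-diagnosis-only fit, a one-time drop looks partly like progressive decline, which overstates the decline. Only the recovery after a short-lived drop is understated there.

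Other objections:
- **Labelling.** Table 1 calls T1 to T10 postdiagnosis, and post-treatment appears only in the description of the span. This stands: the plan does not formally declare T1 a post-treatment assessment. It still attributes T1 scores to RT through the model.
- **Time since treatment.** A lag of this kind is listed among the confounders. It is undefined, is not among the variables named for the weight model, and does not recode a pre-RT survey.
- **Equation 1.** RT carries a time subscript in one term and none in the interaction. A time-varying RT would answer the point, but the level-2 text describes one yes/no value per woman.
- **Unknown extent.** This stands. Neither the diagnosis-to-RT interval nor the RT share is given, so the percentages are illustrations.
- **Exclusion 3 names treatment, not RT.** This stands. It may refer to first treatment, so RT could begin after month 12.

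**Conclusion.** The defect holds at moderate severity. Surveys are timed from diagnosis, RT is fixed per woman, and nothing requires a survey to follow RT, so some T1 surveys of RT women are analysed as outcomes of a treatment not yet given. Up to a third of post-diagnosis surveys lie in the window where this can happen.

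For a persistent effect, with even timing within T1 and RT at 3 to 6 months, the average post-diagnosis level contrast loses about 8-17% and the within-2-year contrast about 12-25%. The evidence does not show dilution of γ11: it is nearly unchanged with T0 in the model. Without T0 it is distorted in a way that depends on the true curve, for example a spurious -0.21 per year for a 3-point drop at 6 months. The assumed interval, curves and 3-point size are not trial figures.

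**What to change.** 1. Keep all 465 women and leave criterion 5 as it is. Requiring a survey at 12 months or later could remove up to 210 women and would condition on surviving and responding to that point.
2. Model T1 (0 to <12 months) as a separate treatment-phase period. Within T1 a single RT coefficient should replace the γ01 and γ11 terms, so that T1 does not feed the RT slope. If RT dates are available, code RT as time-varying instead, and make the subscripts in equation 1 agree.
3. Report a sensitivity analysis that drops T1 surveys and bases the post-treatment RT contrast on t≥12 months.
4. State that exclusion 3 limits treatment and not RT by name, so the 12-month cut makes it likely, not certain, that RT has begun.
5. State whether T0 lies on the fitted line. A straight line through T0 turns a one-time drop into a slope even without T1 (-0.447 per year for the 3-point drop), and the T1 term does not cure that.

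**Cost.** The survey-to-diagnosis intervals are already tabulated, so the work is model wording and one extra analysis. The post-treatment contrast then rests on up to 513 of 766 post-diagnosis surveys, up to 210 women may contribute none of them, and the confidence interval widens.
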